#### Pilot data collection

After the training, all centers will conduct pilot data collection for 2
weeks. This time was based on the previous experience of the TeleICU project
with other pediatric ICUs. The objective is to accompany the collector until
he or she reaches minimum quality conditions and to provide time for
efficiency in data collection to be achieved. This is a form of training and
adaptation for the application of data collection forms. During this time,
the weaknesses of each collector will be identified, and adjustments will be
made according to the specific need of each collector. The centers
participating in the control group will start the official collection after
2 weeks, while the centers participating in the intervention group will have
another 2 weeks of pilot training with the addition of telerounds in their
routine. After this period, the centers will begin the official data
collection. All data from the pilot phase will be excluded from the database
and will be stored based on the rules of the General Data Protection Law
(LGPD - *Lei Geral de Proteção de
Dados*).^(34)^

### Monitoring of data collection

#### Monitoring committees

To ensure the scientific integrity of the study, the protection of
participants and the credibility of the data, in addition to avoiding
conflicts of interest, a steering committee will be formed. The constitution
of this committee will provide overall oversight for the project to ensure
that it is conducted in accordance with the rigorous standards established
in the governance framework for research for health and social care of the
department of health and the Guide to Good Clinical Practice.^(35)^

#### Data collection monitoring team

Data collection will be monitored by a researcher from the project team
(monitor) and a statistician. The team will be composed of three research
monitors, each of whom will be responsible for certain participating centers
and will have direct communication with the collectors of these centers. The
monitors will be responsible for reviewing the data weekly, assessing
whether the inclusion criteria were met, validating the consistency of the
data and verifying that all forms were filled out correctly. For this to be
possible, the statistician of the proposing institution will be responsible
for reviewing the data weekly, sending reports with the inconsistencies
found and necessary adjustments in the collections to the researchers. Figure 2 proposes a detailed flowchart of
this process.

**Figure 2 f2:**
[figure not shown]
Flowchart of monitoring of data collection.

Based on this report, the researchers will open queries in REDCap®
(spaces for requesting the review of information), indicating to the
collectors of the participating centers the inconsistencies found and what
needs to be changed. Once inconsistencies remain, the monitors will inform
the collectors by e-mail, message, telephone calls or videoconference so
that the doubts are clarified and the inconsistencies resolved. There will
also be a follow-up by the monitors regarding the monitoring of the
adherence of the pediatric ICUs in the telerounds for the intervention
group. In addition, these professionals will evaluate the telerounds to
identify possible deviations from the round protocol, as shown in figure 2S
(Supplementary Material).

#### Treatment of missing data

We assume that there will be missing data in the research variables. However,
monitoring will be performed regularly to check for missing data and
inconsistencies, and based on the evidence, the monitors will contact the
collectors to make the necessary adjustments.

Data analyses will be performed with the information that is available after
the monitoring. Thus, the primary and secondary outcomes will not have data
imputation.

### Outcomes

The primary outcome measure will be the length of stay of the patients in the
PICU, defined as the difference between the date of discharge and the date of
admission to the ICU. The secondary outcomes will be mortality rate, IMV-free
days, days using antibiotics, days using vasoactive drugs and days using
sedoanalgesia.

### Statistical analysis

Statistical analyses will be performed both by intention-to-treat and by
protocol, considering that the study design is a cluster RCT, and data from the
observed pediatric ICUs will be analyzed.

The description of the information regarding the PICUs and the characteristics of
the participants will be presented for the control and intervention groups, in
which the categorical variables will be presented by absolute and relative
frequency, while the continuous variables will be first evaluated for normality
by means of visual verification of histogram and Shapiro‒Wilk test and presented
as the mean and SD or median and interquartile range (IQR), depending on the
data distribution, as shown in table 1S (Supplementary Material).

For the primary outcome of the study, a noninferiority analysis will be performed
through modeling, considering that the data are correlated in each ICU, by
generalized mixed models adjusted for variables of interest to the researchers.
Regarding the secondary outcomes, correlated data models will also be used;
however, the probability distribution of each outcome will be taken into
account. Table 2S (Supplementary Material) describes the data to be
analyzed.

Sensitivity analyses will be conducted only for the primary outcome in the
intervention group to verify whether adherence to teleround can impact the
length of stay.

We will also analyze some exploratory results regarding the days of IMV use,
number of days off for each ventilatory support and days off the use of
medications such as antibiotics, sedoanalgesia, antifungal and antiviral, water
balance during hospitalization and verification of permanence in hospital
intensive care (use of IMV or sedoanalgesia) in participants who spent at least
8 days in the pediatric ICU, as shown in table 3S (Supplementary Material).

All statistical analyses will be performed considering a significance level of
0.05. The software to perform all the analyses will be the R program, version
4.2.1 or a later version.

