### Sample size

A total of 16 pediatric ICUs, including 100 participants per location, for a
total of 1,600 participants will be selected to detect a decrease of 2.3 days of
hospitalization in the intervention units compared to the control unit. To
consider the standard deviation (SD), the data from the TeleICU project
indicators were used for a SD of 6.2 days in the control units and 7.1 in the
intervention group, in addition to an intraclass correlation coefficient of
0.05, power of 80% and alpha of 5%. WinPepi software, version 11.65, was chosen
to determine the sample size calculation.

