## CONCLUSION

This protocol presents an innovative panorama because it not only proposes
telemedicine in intensive care but also uses this tool to promote equity in regions
where there is a lack of specialized professionals in PICUs and for continuing
education in places far from large centers in Brazil. Thus, it represents a research
scenario little explored thus far. If telemedicine shows positive clinical care
results in relation to conventional treatment, more pediatric patients may benefit
from the technology as a form of intensive health care.

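### The primary analysis is called noninferiority, but the trial is sized and justified to show a 2.3-day shorter stay; the two hypotheses must be reconciled

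*Protocol article*

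**What the plan says.** The Statistical analysis section states: "For the primary outcome of the study, a noninferiority analysis will be performed". The model is to be one of the "generalized mixed models adjusted for variables of interest to the researchers", allowing for correlation within each ICU. The section sets a significance level of 0.05 and plans both intention-to-treat and per-protocol analyses. It gives no margin and no confidence-limit rule.

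The Sample size section describes 16 pediatric ICUs with 100 participants each, a sample "selected to detect a decrease of 2.3 days of" PICU stay under telemedicine relative to control. The planning SDs, taken from the project's own indicators, are 6.2 days (control) and 7.1 days (intervention). The ICC is set at 0.05, with 80% power and a 5% alpha.

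The Context and rationale section presents telemedicine as a tool that shortens ICU stay. The Objectives and Discussion sections are neutral: they speak of evaluating length of stay and the impact of telemedicine. The word noninferiority appears only in the Statistical analysis section.

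**The concern.** Detecting a decrease means testing a null hypothesis of no difference, and success means showing a shorter stay. Noninferiority means testing a null hypothesis that the intervention is worse by at least some margin, and success means ruling out that much worsening. The nulls differ, and so do the criteria for success.

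The design makes the difference matter. The intervention adds telerounds, on-demand specialists and continuing education, and is compared with usual care alone. It replaces nothing that might be given up in exchange for a tolerable loss. A finding that stay is not much longer than under usual care would not answer the question the trial was sized for.

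An analyst who follows the Statistical analysis section literally would run a test that can succeed when stay is unchanged or somewhat longer. A reader of the Sample size section would expect success to mean a reduction.

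**Working it through.** **Inputs (Sample size and Study design sections).** SD 6.2 days (control) and 7.1 days (intervention); ICC 0.05; 100 participants per cluster; 16 clusters at 1:1, so 8 per arm; difference 2.3 days; power 80%; alpha 5%. Sidedness is not stated.

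**Step 1. Reproduce the stated sample size as superiority.**
- Sum of variances: 6.2² + 7.1² = 38.44 + 50.41 = 88.85.
- Independent n per arm, two-sided 5%, 80% power: (1.960 + 0.842)² × 88.85 / 2.3² = 131.8, so 132.
- Design effect: 1 + (100 − 1) × 0.05 = 5.95.
- Inflated: 132 × 5.95 = 785 per arm = 7.85 clusters, rounded up to 8. Total 2 × 8 × 100 = 1,600, as stated.
- Power at 8 × 100 per arm: 80.8% (normal approximation).
- A one-sided 5% test gives 104 × 5.95 = 619 per arm, hence 7 clusters per arm and 1,400 in total. That does not reproduce the plan.

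So the plan's number follows from a two-sided superiority calculation, and no margin enters it.

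**Step 2. Precision of the planned trial.** SE of the difference = √(88.85 × 5.95 / 800) = 0.813 day. The 95% CI half-width is 1.96 × 0.813 = 1.59 days (normal), or 2.145 × 0.813 = 1.74 days (t, 14 df).

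**Step 3. What a noninferiority result would mean.** The article gives no margin, so every margin M below is an assumption. The test is one-sided 2.5%, and the true difference δ is intervention minus control. The normal version is P(noninferior) = Φ((M − δ)/SE − 1.96). The t version uses a noncentral t with 14 df and noncentrality (M − δ)/SE.

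| Assumed M (days) | True δ (days) | (M − δ)/SE | P, t 14 df | P, normal |
|---|---|---|---|---|
| 2.3 | 0 | 2.83 | 75% | 81% |
| 2.3 | +1 | 1.60 | 32% | 36% |
| 1.0 | 0 | 1.23 | 21% | 23% |

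**Step 4. How N would depend on the margin if noninferiority were kept** (δ = 0, one-sided 2.5%, 80% power, clusters of 100, normal approximation).

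| Assumed M (days) | Per arm | Clusters per arm | Power at 16 × 100 |
|---|---|---|---|
| 1.0 | 4,154 | 42 | 23% |
| 1.5 | 1,845 | 19 | 45% |
| 2.0 | 1,042 | 11 | 69% |
| 2.3 | 786 | 8 | 81% |
| 3.0 | 465 | 5 | 96% |

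**The case against.** **The margin may be fixed elsewhere.** This is a condensed article. The full protocol, the SAP and the supplementary tables are not shown. A reader might infer that no margin exists and that the threshold could be picked after the data are seen. The documents do not support that inference, and the absent margin is not a defect in its own right here. The conflict remains, because a margin stated elsewhere would not turn a decrease to be detected into a tolerated increase.

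**2.3 days could be the margin.** The arithmetic allows it: 786 per arm at zero true difference and one-sided 2.5%, against 785 for superiority. It would therefore be too strong to say that the stated 80% power cannot belong to a noninferiority test. The number does not separate the two readings; the wording does. The Sample size section calls 2.3 days a decrease in the intervention units.

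**The pass rates are not error rates.** This is correct. A high chance of declaring noninferiority at zero effect is the intended power of such a test, and a 1-day increase lies inside a 2.3-day margin. The figures show that noninferiority answers a different question. They do not measure harm under the actual plan.

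**Superiority intent is not explicit.** The aims are neutral. The Conclusion's statement that with positive "results in relation to conventional treatment, more pediatric patients may benefit" is general and does not name length of stay. Planning both intention-to-treat and per-protocol analyses is common in noninferiority trials, though not confined to them. A deliberate choice of noninferiority cannot be excluded, so the alternative repair is offered below. The direction still comes clearly from the sample size and the rationale.

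**Conclusion.** The point holds as an internal contradiction: the primary test named in the Statistical analysis section does not match the hypothesis on which the Sample size section rests. As written, the test is wrong for the stated target and must be corrected before analysis.

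The contradiction itself needs no assumption, since both statements are printed in the article. The illustrative size (75–81% and 32–36%) rests on an assumed 2.3-day margin, a one-sided 2.5% test and the plan's own SDs, ICC and cluster numbers. Another margin would give other figures.

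The sample size is not shown to be in error. It reproduces under the normal approximation. With a t reference on 14 df, superiority power at 16 × 100 is 74.9%, which is a separate matter from this point.

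**What to change.** In the Statistical analysis section, replace the noninferiority analysis with a two-sided 5% superiority test of the intervention effect on PICU length of stay. Estimate the effect from the cluster-adjusted mixed model, by intention to treat, and report it with a 95% CI. Success means that the CI excludes no effect in the direction of shorter stay: entirely below 0 if the model yields a difference, entirely below 1 if it yields a ratio. The Eligibility section excludes intervention-cluster patients who did not receive telemedicine, so the intention-to-treat set needs to be stated consistently with this test.

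The cost is a change to one sentence, carried into the analysis plan. The sample of 1,600 and the 2.3-day planning difference stay as they are.

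If noninferiority is truly intended, the Sample size section must instead state and justify a margin and derive N and power from it. That could be costly: for example, an assumed 1-day margin would need 42 clusters of 100 per arm rather than 8.

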## ETHICS AND DISSEMINATION

### Ethical approval and consent to participate

This study will be conducted in accordance with resolution 466/12 of the National
Health Council^(36)^ and was
approved by the Research Ethics Committee (REC) of the proposing institution.
Subsequently, the project will be submitted to the RECs of the participating
centers.

The parents or guardians of the study participants will be asked to sign an
informed consent form. Participants ages 6 through 18 will be required to sign
an informed consent form. When a patient is unable to consent to participate in
the study due to clinical limitations, he or she will be asked to sign a waiver.
In addition, rights to use images will be requested.

### Dissemination

The study is expected to make results widely available by disseminating findings
in conference presentations and publishing articles in high-impact journals.
Moreover, it is expected that the evidence may serve as a basis for the creation
of public policies that allow for more adequate and specialized care in all
pediatric ICUs in Brazil, even those with a lack of professionals specializing
in intensive care or pediatrics.

In addition, through the dissemination of this protocol, we will seek to
encourage the reproducibility of similar studies in realities of access to
health care different from those found in Brazil so that the potential of
telemedicine can be more widely verified and the results of this intervention
can be measured in different socioeconomic, cultural and health contexts.

## DISCUSSION

This article describes the protocol of the TeleICU project, which is a multicenter,
clustered, open-label RCT study. The main objective is to evaluate the impact of
telemedicine on clinical care indicators.

The present study has the potential to reproduce studies on telemedicine in intensive
care and may make important contributions to ICU care in Brazil and in other
settings. In addition, the study will introduce telemedicine as a way to train
professionals who work in ICUs, even those who are not intensivists, as occurs in
many Brazilian units. Thus, the study proposes a model that offers benefits when
incorporated into the SUS.

The limitations of this protocol relate to the time difference between the
participating centers for the start of activities. This is due to the impossibility
of controlling the procedures of the respective ethics committees in the processes.
In addition, dependence on internet resources impacts the occurrence of telerounds
only and exclusively at the bedside. In this sense, we considered this factor to
intervene in the analysis of the study.

## CONCLUSION

This protocol presents an innovative panorama because it not only proposes
telemedicine in intensive care but also uses this tool to promote equity in regions
where there is a lack of specialized professionals in PICUs and for continuing
education in places far from large centers in Brazil. Thus, it represents a research
scenario little explored thus far. If telemedicine shows positive clinical care
results in relation to conventional treatment, more pediatric patients may benefit
from the technology as a form of intensive health care.
